## Methods: Participants, interventions and outcomes

### Study setting {9}

The study will take place in the UK, at the Infantry Training Centre, Catterick, North Yorkshire and a nearby National Health Service (NHS) institution within the County Durham and Darlington NHS Foundation Trust, neither of which are part of the University of East Anglia.

### Eligibility criteria {10}

Men and women, aged 18–40 years, with single or multiple lower body stress fractures, diagnosed by MRI a maximum of 7 days before date of consent, will be eligible to participate. Potential participants must be undergoing Phase One or Two Army training (i.e. initial or trade training) and will, therefore, have recently passed a physician-screened medical assessment. Eligible participants must provide written informed consent and be able to comply with the study protocol, adhere to study visit requirements, and have baseline safety blood test results within adult reference ranges (analytes listed in Table 1).

**Table 1 Tab1:** Blood and urine biochemistry

		Baseline only	Baseline and weeks 4, 8, 12, 16, 20 and 24
**Blood**	**Safety**	Haemoglobin Platelets White blood cell count Absolute neutrophil count Urate Albumin Bilirubin Alanine aminotransferase Alkaline phosphatase Glucose Parathyroid hormone	Calcium Phosphate Magnesium Sodium Potassium Urea Creatinine High- and low-density lipoproteins Total cholesterol
	**Research**		Parathyroid hormone (including 1-34 and other fragments) Cyclic adenosine monophosphate Vitamin D metabolites Bone remodelling compounds: Carboxyl-terminal collagen cross-links Procollagen type 1 N-terminal propeptide Sclerostin Osteoprotegerin Receptor activator of nuclear factor kappa-B ligand Dickkopf-related protein 1 Fibroblast growth factor 23 Butyrate
**Urine**	**Safety**		Calcium Phosphate
	**Research**		Pyridinoline Deoxypyridinoline Oxalate Cyclic adenosine monophosphate

Additional bone remodelling compounds may be analysed if assay methodologies are validated during the trial

Potential participants will be excluded if they have any of the following: known hypersensitivity to active parathyroid hormone or any excipients listed in the summary of product characteristics [24]; pre-existing hypercalcaemia; a history of skeletal malignancies or bone metastases; any contraindications that would prevent them from undergoing an MRI scan; severe renal impairment (participants with a moderate renal impairment will be treated with caution at the Principal Investigator’s discretion and in accordance with the summary of product characteristics [24]); metabolic bone diseases, including a pre-existing diagnosis of hyperparathyroidism or Paget’s disease of bone; an unexplained elevation of alkaline phosphatase; prior external beam or implant radiation therapy to the skeleton; depression, identified by the Columbia-Suicide Severity Rating Scale (C-SSRS); or are receiving digoxin or any other concurrent therapy that would interfere with the evaluation of the safety or efficacy of teriparatide; currently pregnant, suspect they are pregnant, or are breastfeeding; present with open epiphyses in their diagnostic MRI scan; or are participating in a concurrent drug trial. Potential participants will be excluded if they are in receipt of an investigational drug or biological agent within the 4-week period prior to study entry (or five times the half-life if this is longer). Participants can be entered into other observational studies given prior agreement from the Trial Management Groups (TMGs) of both studies. Women must have a negative serum pregnancy test at baseline and agree to use a highly effective form of contraception (with a failure rate < 1% per year) for the duration of their participation in the study.

Principal Investigators (or medically trained delegates) will be appropriately qualified and licensed to practice within their trial site. Suitably trained staff will undertake delegated trial activities. All investigators will sign an investigator statement to confirm they will comply with the study protocol. Sites responsible for prescribing and dispensing drugs will have a pharmacy that is able to store, prepare and dispense drugs appropriately.

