**Fig. 1 Fig1:**
[figure not shown]
Overview of the trial design, interventions and assessments. ^1^Serum 25-hydroxyvitamin D < 30 nmol/L, deficient; ≥30 nmol/L, not deficient; ^2^Pregnancy test for all at baseline, week 16 and 24, and four-weekly for participants allocated to the intervention arm; ^3^Weekly visual analogue scale; ^4^Short Form (36) Health Survey; ^5^Dual-energy X-ray absorptiometry (DXA) scan of the lumbar spine and hips (baseline and week 16 only); peripheral quantitative computed tomography (pQCT) scan of the diaphyseal tibia; and high-resolution pQCT (HR-pQCT) scan of the metaphyseal tibia and radius; ^6^Accelerometer worn 24 h/day and replaced four-weekly; ^7^Columbia-Suicide Severity Rating Scale (C-SSRS) for all at baseline, and four-weekly for participants allocated to the intervention arm; ^8^Review of Army fitness records; ^9^Magnetic resonance imaging (MRI) scans to cease when fracture is radiologically healed; ^10^Clinical assessments twice weekly after fracture is radiologically healed, and to cease when fracture is clinically healed; ^11^Review of Army medical records

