### Criteria for discontinuing or modifying allocated interventions {11b}

Participants may stop their treatment with teriparatide at any time if they wish. For safety reasons, treatment will be discontinued for individual participants if they experience an unacceptable adverse event or treatment toxicity; an intercurrent illness that prevents further treatment; any change in their condition that in the clinician’s opinion justifies ceasing treatment; or any contraindication to continuing treatment within the summary of product characteristics, including pregnancy [24]. Participants who have their treatment interrupted for 2 weeks or more, intentionally overdose, or exhibit signs of depression (indicated by the C-SSRS completed every 4 weeks prior to teriparatide re-dispensing) will also have their treatment discontinued. Discontinuation of treatment with teriparatide will not be a reason for withdrawal from the study, and participants will complete follow-up visits provided they are willing. Where pre-dose serum calcium is found to be above the upper limit of normal, treatment will be withheld until serum calcium returns to normal and restarted every other day, or every third day according to the clinical judgement of the treating clinician and Chief Investigator. Before restarting treatment, the participant’s correct use of the injection pen will be verified, and differential diagnoses will have been excluded (e.g. primary hyperparathyroidism, excess vitamin D and malignancy). Where pre-dose serum calcium is < 2 mmol/L, treatment will continue with the addition of twice daily calcium (1500 mg) and vitamin D (400 IU) supplementation.

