## Data collection and management

### Plans for assessment and collection of outcomes {18a}

Investigators will be trained centrally in the use of data collection instruments, laboratory equipment, questionnaires, case report forms, and data entry onto a central database. Investigators will follow standard operating procedures and working instructions to help ensure valid and reliable data are collected. Standardising these processes will enhance data quality and reduce bias by detecting and reducing the quantity of missing or incomplete data, inaccuracies, and excessive variability in measurements [47]. Screening and eligibility data will be collected by investigators using case report forms prior to allocation (Fig. 2). Radiological healing will be assessed by two musculoskeletal consultant radiologists blind to the randomisation outcome, using Fredericson grading of MRI [39, 40], and will be recorded using case report forms. Clinical healing will be assessed by investigators using a standardised protocol and case report form [41]. The date of the initial decision to discharge from Army physical rehabilitation will be obtained from participants’ Army medical records and recorded by investigators using case report forms. The SF-36 questionnaire will be completed by participants to assess health-related quality of life [44, 45], and investigators will verbally ask participants the questions in the C-SSRS questionnaire to assess depression. Participants will record their pain on a visual analogue scale [42, 43]. Investigators will ask participants to report adverse events and their use of concomitant medications, which will be recorded using case report forms. Participants’ alcohol consumption and smoking habits will be recorded by investigators completing case report forms. In accordance with standard operating procedures, physical activity levels will be assessed using accelerometers (in a minimum of 10 participants in each of the control and intervention arms), venous blood samples will be collected by investigators, urine samples will be collected by participants, and blood and urine biochemistry will be analysed by technicians blind to the randomisation outcome (Table 1). Pregnancy tests will be conducted according to standard operating procedures. Bone density and morphology will be assessed by investigators using DXA, pQCT and HR-pQCT, according to standard operating procedures, with a random sample of analysed images (≥ 10%) reviewed at the end of the study by an independent assessor blind to the randomisation outcome. Physical fitness will be recorded by investigators accessing participants’ Army fitness records. Army medical records will be reviewed by investigators to record any subsequent bone injuries and fractures.

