Teriparatide should not be given to individuals with open epiphyses [24]; thus, potential participants who present with open epiphyses in their diagnostic MRI scan will be excluded from participating. Signs of depression will be monitored using the C-SSRS because depression is a possible side effect of treatment with teriparatide [24]. Women will require a negative serum pregnancy test result to be eligible to participate and must agree to use of a highly effective form of contraception (failure rate < 1% per year, e.g. combined oestrogen and progestogen, or progestogen-only hormonal contraception, or intrauterine device) because teriparatide is contraindicated for use during pregnancy [24]. Treatment with teriparatide will be discontinued for participants who become depressed or pregnant. A negative urine pregnancy test result will be required prior to teriparatide re-dispensing. Dual-energy X-ray absorptiometry, pQCT, and HR-pQCT scans will expose participants to ionising radiation, however, the total radiation exposure for each participant will be relatively low, categorised as minor risk (0.1–1 mSv; Category IIa) [53]. A negative pregnancy test result will be required before DXA, pQCT, and HR-pQCT scans to avoid exposing pregnant women to ionising radiation.

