### Protocol amendments

The following amendments were approved by MODREC, resulting in the current study protocol described here (version 1.6). In June 2019, during the planning stage, the study was changed from a double blind, placebo-controlled trial to an open label design, with usual Army standard care as the control arm. The principal reason for this change was the rejection of return to training as a potential primary endpoint, since readiness to return to training was considered too subjective, and the subsequent choice of an objective primary endpoint of improvement in radiological healing assessed by MRI. There is no known biological mechanism by which participants can influence radiological measures of stress fracture healing, therefore, this objective endpoint lends itself to an open label design. A second reason was the continued unavailability of a suitable placebo. An open label design has the added benefits of reducing the burden on control arm participants by removing the requirement for them to administer daily injections of placebo for 24 weeks, and avoids the possible ethical implications of requiring them to do so; it may also increase compliance within the intervention arm since participants will know they are receiving active drug. The practical issue of adherence to the injection regime by military recruits, knowing they are receiving drug, is important for the future roll out of any treatment regime. Additional amendments were the protocol for calcium and vitamin D supplementation where serum calcium is < 2 mmol/L; the requirement for participants to be prescribed vitamin D as part of their standard care (if vitamin D deficient); MRI scans at weeks 20 and 24, where a fracture remains unhealed at week 16; a subgroup of participants to wear accelerometers to assess their physical activity levels; and clarification regarding randomisation whereby allocation will be stratified by vitamin D status and single or multiple lower body stress fracture sites.

In August 2019, during the study planning stage, the exclusion criteria were modified to exclude potential participants with depression, indicated by the C-SSRS, and to add the provision that participants who exhibit signs of depression (as indicated by the C-SSRS) will have their teriparatide treatment discontinued.

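### The entry exclusion and the scheduled four-weekly check for depression rest only on the C-SSRS, by its printed name a suicide severity scale, although the stated hazard is depression

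*Protocol article*

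**What the plan says.** The Eligibility criteria {10} list, among the exclusions, "depression, identified by the Columbia-Suicide Severity Rating Scale (C-SSRS"). No other means of identifying depression at entry is given.

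During treatment, section {11b} discontinues teriparatide for participants who "exhibit signs of depression (indicated by the C-SSRS completed every 4 weeks prior to teriparatide re-dispensing"). Section {18a} describes how the scale is used: "investigators will verbally ask participants the questions in the C-SSRS questionnaire to assess depression". The Fig. 1 legend gives the schedule: "Columbia-Suicide Severity Rating Scale (C-SSRS) for all at baseline, and four-weekly for participants allocated to the intervention arm".

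The Safety section gives the reason: "Signs of depression will be monitored using the C-SSRS because depression is a possible side effect of treatment with teriparatide". The same section adds, without naming any tool, that a participant who becomes depressed or pregnant is taken off treatment.

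The Protocol amendments section shows that both rules were introduced deliberately in August 2019: "the exclusion criteria were modified to exclude potential participants with depression, indicated by the C-SSRS", together with the provision that "participants who exhibit signs of depression (as indicated by the C-SSRS) will have their teriparatide treatment discontinued".

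**The concern.** The hazard named is depression, while the instrument named is, by its printed title, a rating of suicide severity. A person can be depressed without being suicidal. If the scale measures what its title says, the entry criterion and the scheduled check look for something narrower than the condition they are meant to catch.

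What is at stake is participant safety. A recruit with non-suicidal depression could be enrolled without meeting the depression exclusion, be allocated to teriparatide, and pass each scheduled check while taking a drug that the protocol itself links to depression. Such a case would come to light only through the trial's general safeguards.

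This is not detail left to a fuller document. The article states which tool defines the condition, and does so consistently.

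**Working it through.** The plan gives no figure on this point, so the check sets every statement about depression side by side.

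| Place | Step | Condition named | Tool named |
|---|---|---|---|
| Eligibility criteria {10} | Entry exclusion | Depression | C-SSRS |
| Section {11b} | Four-weekly, before re-dispensing | Signs of depression | C-SSRS |
| Section {18a} | How the assessment is made | Depression | C-SSRS |
| Safety, monitoring sentence | Purpose of monitoring | Depression as a side effect | C-SSRS |
| Safety, discontinuation sentence | Stopping | Becoming depressed | None |
| Protocol amendments, exclusion | Entry exclusion | Depression | C-SSRS |
| Protocol amendments, stopping | Stopping | Signs of depression | C-SSRS |

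**Count.** The five sections contain 1 + 1 + 1 + 2 + 2 = 7 statements. Six name the C-SSRS, one names no tool, and none names another instrument or criterion. All five sections name the C-SSRS at least once.

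**Entry.** The exclusion is defined by the scale alone. The eligibility section also says that recruits will recently have passed a medical assessment for Army training, but that precedes the trial and is not described as covering depression. The printed exclusion list contains no separate clause for depression judged clinically.

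**Scheduled check.** Two conditions are checked before re-dispensing. For pregnancy the check is a test of the condition itself: "A negative urine pregnancy test result will be required prior to teriparatide re-dispensing". For depression it is the C-SSRS.

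**Stopping.** Here there are routes that do not depend on the scale. The unqualified sentence in Safety ends treatment for anyone who becomes depressed. Section {11b} also allows stopping for an unacceptable adverse event, or for any change that the clinician thinks warrants it. Depression that someone notices can therefore already end treatment. What the plan lacks is a scheduled step that looks for it.

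**SF-36.** Its mental health domain is collected at baseline and every four weeks, but {18a} assigns the questionnaire to quality of life. It plays no part in either rule.

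**Size.** The number of missed cases is the number of depressed recruits multiplied by the share whom the scale would not flag. The article gives neither quantity, so no estimate is possible.

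**The case against.** The strongest objection is that a title is weak evidence of content. The article does not reproduce the C-SSRS items, version or cut-off, so whether a depressed but non-suicidal recruit would really pass cannot be tested from it. Working instructions may also say how answers become signs of depression. This stands as a limit: it rules out any estimate and any claim that the scale cannot detect depression. It does not remove the mismatch between the printed purpose and the printed name of the tool.

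The second objection concerns safeguards. Investigators ask about adverse events, no adverse event is exempt from reporting, all participants are seen at least every four weeks, and face-to-face reminders accompany each re-dispensing. These are real, and they keep the severity low. None is a check for depression tied to entry or to dispensing, and the August 2019 amendment added depression rules of its own.

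A reader might infer something stronger: that every decision to stop treatment turns on a suicide scale, so that a depressed recruit must stay on the drug. The documents do not support this. The discontinuation sentence in Safety names no tool, and {11b} leaves room for clinical judgement.

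**Conclusion.** The point holds for the entry exclusion and for the scheduled four-weekly check, both of which identify depression solely by a scale named for suicide severity. It holds only weakly for stopping, where depression recognised by any route can already end treatment.

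The conclusion assumes that the scale measures what its printed name says and that the article reports the rules as they operate. Severity is low: general safeguards exist and the number of cases affected is unknown. The primary analysis and the sample size calculation are untouched. The change is still worth making, because the protocol identifies depression as a possible drug side effect and the remedy fits into existing visits.

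**What to change.** - **Eligibility criteria {10}:** replace the single item with two: *suicidal ideation or behaviour on the C-SSRS*, and *current depression in the judgement of the investigator or medically trained delegate*.
- **Section {11b}:** discontinue teriparatide for either reason. Add a brief mood question to the existing four-weekly intervention-arm check before re-dispensing, and refer any positive answer to the clinician.
- **Section {18a} and Safety:** describe the C-SSRS as assessing suicidal ideation and behaviour, and depression as assessed by the mood question and clinical judgement.

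The SF-36 mental health domain should not be made a trigger, since the article gives no level at which it would act.

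The cost is amended wording in four places, one short question at visits already scheduled, some false-positive clinical reviews and possibly a few more exclusions. Because the question is asked in one arm only, as the repeat C-SSRS already is, depression found through it should not be compared between arms as if both had been asked equally.

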### Who will take informed consent? {26a}

Written informed consent will be obtained by an appropriately trained clinician or delegated member of staff at the NHS institution in person, or remotely (consent form completed by the participant during a telephone or video call) if NHS hospital visits are restricted for any reason. Potential participants will be provided with a participant information sheet and will be invited to meet investigators for a detailed explanation of the study’s aims, methods, benefits and potential hazards. Consent will be obtained a minimum of 24 h after the potential participant receives the participant information sheet and detailed explanation of the study; and a maximum of 7 days after their diagnosis with a lower body stress fracture using MRI. Consent will be obtained in the absence of the participants’ Army Chain of Command, and it will be explained to potential participants that choosing to take part, or not, or choosing to withdraw from the study at any point, will have no bearing on their future Army training or career. Potential participants who wish to take part will provide informed consent before any trial-specific procedures are undertaken. Participants will be invited to provide additional consent to wear an accelerometer for the duration of their participation in the study, however, this is optional, and participants may refuse whilst remaining eligible to take part.

### Additional consent provisions for collection and use of participant data and biological specimens {26b}

Participants will be asked to consent to their samples being stored securely in a pseudoanonymised form for use in future studies, pending ethical approval. No ancillary studies are planned.

## Interventions

### Explanation for the choice of comparators {6b}

There are no current pharmacological therapies indicated for the treatment of stress fractures. The control arm will receive usual Army standard care. Participants will commence a period of physical rehabilitation under the supervision of a physiotherapist and Army exercise rehabilitation instructor, in accordance with standard Army procedures. The intervention arm will receive 20 μg/day of teriparatide by subcutaneous injection in addition to usual Army standard care. This is the only licensed dose for teriparatide in Europe. Teriparatide is licensed for the treatment of osteoporosis in postmenopausal women and in men at increased risk of fracture, and the treatment of osteoporosis associated with sustained systemic glucocorticoid therapy in women and men at increased risk for fracture [24]. An open label design was chosen for a number of reasons: (i) the aims of the study and objective primary endpoint indicated an open label design; (ii) it was not possible to procure a matched placebo; (iii) there will be no requirement for control arm participants to administer themselves with daily injections of placebo for up to 24 weeks, thereby reducing the burden on them, and avoiding the possible ethical implications of requiring them to do so; and (iv) adherence to the injection regime may be improved with intervention arm participants knowing they are receiving active drug. The practical issue of adherence to the injection regime by military recruits, knowing they are receiving the drug, is of importance to the Ministry of Defence and the future roll-out of any treatment regime.

